#### Cost-effectiveness study

A healthcare funder perspective will be used for the economic evaluation. Health outcomes will be measured in terms of falls prevented. Costs will include healthcare utilization collected by monthly calendars in intervention and control participants and intervention costs (including staff, training, capital costs, and consumables). Mean costs and the mean health outcomes in each trial arm will be calculated. The incremental cost-effectiveness ratio of the intervention compared to control group will be calculated as the cost per fall prevented; results will be plotted on a cost-effectiveness plane. Bootstrapping will be used to estimate a distribution around costs and health outcomes and to calculate the CIs around the incremental cost-effectiveness ratios. One-way sensitivity analysis will be conducted around key variables and assumptions; a probabilistic sensitivity analysis will be used to examine joint uncertainty in all parameters. A cost-effectiveness acceptability curve will be plotted to provide information about the probability that the intervention is cost-effective, given decision makers’ willingness to pay for each fall prevented.

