### Effectiveness trial methodology

A two-arm cluster randomized controlled parallel trial is being conducted with the general practice as the unit of randomization and outcomes measured at both practice change and patient outcome levels. Cluster randomization is used in order to avoid contamination among patients of the same GP because the intervention is delivered by the GP. Randomizing GPs within the same practice to the same arm likewise avoids contamination among GPs. The trial is being conducted according to CONSORT guidelines [32]. Figure 1 provides a flow chart of participants through the cluster trial, and Table 2 summarizes the research questions and measurements. Recruitment commenced in June 2015.

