#### Sample size estimate

This cluster randomized trial of 560 patients from 28 GP practices is designed to have 80% power to detect as significant at the two-sided 5% level a 15% between group differences in the proportion of participants falling, from 50% in the control group to 35% in the intervention group (30% relative reduction). We have assumed 50% will fall in the control group, based on previous trials. A reduction to 35% is feasible, as a reduction of this size was found in a previous meta-analysis [33]. Assuming a cluster size of 20 participants per GP practice, an intra-cluster correlation coefficient (ICC = 0.01) and a 15% loss of patients, we require 26 clusters with a total of 520 patients. In all, 28 GP practices (560 patients) will be recruited to allow for possible loss of whole practices during the 12-month follow-up.

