#### Data analysis plan

Data analysis will be on an intention-to-treat basis. For the primary analysis of falls, negative binomial regression will be used to compare the total number of falls per person in the two groups, using an offset for exposure time and accounting for clustering. GP engagement in fall prevention management and GP referral practices will be assessed using questions 11 and 12, respectively, of the 12-month GP survey and corresponding questions on the baseline survey. For management, a score from 0 to 3 will be allocated to each of the first three items and summed to give a total out of 9. The total score for each GP at 12 months will be compared between groups using regression analysis with baseline score as a covariate and adjusting for clustering by GP practice. For referral practice, the number of types of practitioners (out of 13 possible) to whom a GP sometimes or often refers older patients at risk of falling will be counted. The change from baseline for each GP will be compared between groups using Poisson regression, adjusting for clustering by GP practice. Change in Drug Burden Index will be calculated for each patient and compared between groups using regression analysis, controlling for any baseline differences in risk factors (age, gender, comorbidities, hospitalization in past year, and use of walking aid) and accounting for clustering.

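### The cost-effectiveness analysis does not carry over the clustering and exposure-time handling of the primary falls analysis, so its certainty and its falls-prevented figure may not match the trial's own result

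*Protocol article*

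**What the plan says.** Under Effectiveness trial methodology, the protocol article describes a cluster trial "with the general practice as the unit of randomization and outcomes measured at both practice change and patient outcome levels". The Sample size estimate uses "an intra-cluster correlation coefficient (ICC = 0.01) and a 15% loss of patients".

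The Data analysis plan names clustering in all four of its analyses: falls, the GP management score, the GP referral count and the Drug Burden Index. Falls are modelled by negative binomial regression, "using an offset for exposure time and accounting for clustering".

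The Cost-effectiveness study section then gives a separate recipe for the same falls data. "Mean costs and the mean health outcomes in each trial arm will be calculated"; the ratio is the cost per fall prevented; and "Bootstrapping will be used to estimate a distribution around costs and health outcomes and to calculate the CIs around the incremental cost-effectiveness ratios". A cost-effectiveness plane and an acceptability curve follow. The section names no resampling unit, no allowance for practice, no exposure time, and no link to the negative binomial model.

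**The concern.** Two features of the design that the effectiveness analyses respect are not carried into the economic analysis.

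- **Clustering.** About 20 patients share a practice, and the practice was randomized. A bootstrap that draws patients one at a time treats them as independent and understates the variance of both falls and costs. The acceptability curve is a probability statement addressed to a funder, so understated variance makes it look more decisive than the data allow.
- **Exposure time.** The primary model corrects for differing follow-up. A raw arm mean does not: a patient who leaves early has fewer recorded falls, which counts as fewer falls. One report could then contain two falls effects from one dataset.

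**Working it through.** **1. The plan's own clustering figures.** Inputs from the Sample size estimate: 50% versus 35% falling, two-sided 5%, 80% power, 20 patients per practice, ICC 0.01, 15% loss.
- Two proportions with continuity correction: 183 per arm, 366 in total.
- Design effect: 1 + (20 − 1) × 0.01 = 1.19.
- 366 × 1.19 / 0.85 = 512.4 patients; 512.4 / 20 = 25.6, rounded up to 26 practices, or 520 patients.

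This reproduces the stated size. Without the continuity correction the result is 170 per arm, 476 patients and 24 practices, which does not.

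**2. Effect of ignoring practice, closed form.** If patients are treated as independent, the standard error is too small by a factor 1/√DE, and a nominal 95% interval covers 2Φ(1.96/√DE) − 1.
- ICC 0.01, 20 per practice: DE 1.19; interval 8.3% too narrow; coverage 92.8%.
- ICC 0.01, 17 per practice (20 × 0.85): DE 1.16; 7.2% too narrow; coverage 93.1%.
- Other ICCs, assumed because the document gives none for costs, 20 per practice: 0.005 gives 93.9%; 0.02 gives 90.5%; 0.05 gives 84.0%; 0.10 gives 75.0%.

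**3. Which outcome the 0.01 belongs to.** In the sample size it applies to the proportion who fall. The economic outcome is the number of falls. Assume means of 1.0 and 0.7 falls, negative binomial dispersion 1, and a practice effect with SD 0.20 on the log rate. The ICC for any fall is then 0.0098, in line with the protocol. For the count in the control arm:
- between-practice variance: 1.0² × (e^0.04 − 1) = 0.0408;
- within-practice variance: 1.0 + 1.0² × e^0.04 = 2.0408;
- ICC = 0.0408 / 2.0816 = 0.020.

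The same steps for mean 0.7 give 0.016. With 17 patients per practice, DE = 1 + 16 × 0.020 = 1.31 and 1 + 16 × 0.016 = 1.26, and coverage is 91-92%.

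**4. Simulation under the same assumptions** (14 practices × 17 patients per arm; 1,500 trials, 400 bootstrap replicates; falls difference, nominal 95%):

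| Practice SD | ICC, any fall | Patients resampled | Practices resampled, simple | Practices resampled, small-cluster scaling and t quantile |
|---|---|---|---|---|
| 0.20 | about 0.01 | 90.5% | 92.3% | 95.1% |
| 0.30 | about 0.02 | 87.4% | 92.0% | 95.1% |
| 0.45 | about 0.045 | 79.7% | 90.9% | 94.6% |

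Other runs of this set-up gave 90-92%, 86-90% and 78-80% for patient resampling. If 0.01 is instead placed directly on the fall count, patient resampling covered 93.9% and simple practice resampling 92.5%, so there the simple practice bootstrap gains nothing.

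**5. Exposure time.** Assume rates of 1.0 and 0.7 falls per person-year, a true difference of 0.300, with leavers contributing half a year. Raw falls prevented per person = 1.0 × (1 − loss in control / 2) − 0.7 × (1 − loss in intervention / 2).
- 15% in both arms: 0.925 − 0.6475 = 0.278; the ratio of falls stays at 0.70.
- 10% control, 20% intervention: 0.95 − 0.63 = 0.320.
- 20% control, 10% intervention: 0.90 − 0.665 = 0.235.

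**The case against.** The strongest reply is that the section is silent rather than wrong. A bootstrap that resamples practices fits every word of it, and a mean outcome per arm could be a mean rate or a model-based mean. This is one paragraph of a journal article, and resampling details are commonly left to an economic analysis plan. Patients who do not return a calendar are telephoned, which limits missing falls data. At the planned ICC the gain from simple practice resampling is small, under two points in the table.

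Much of this stands. A reader might infer that the plan specifies a patient-level bootstrap and that its intervals are therefore too narrow. The document does not say so; both statements are conditional on the resampling unit. A reader might also infer that the ratio will shift a good deal because of dropout. That needs loss that differs between arms, of which the protocol says nothing, and an incremental cost that stays fixed. Healthcare use comes from the same calendars, so lost follow-up changes the costs as well. Nor can strong clustering of costs be read off the document: GP training and tools are delivered through practices, which makes some clustering plausible, but no amount or between-practice variation is given.

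What does not stand is that condensation alone explains the gap. The preceding section of the same article states the clustering adjustment four times and the exposure offset once. The economic section then fixes a different estimator for the same falls without either. Followed literally, it departs from the primary analysis.

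**Conclusion.** The point holds in conditional form. The economic analysis rests on arm means and a bootstrap with no stated allowance for practice or exposure time. If patients are resampled singly, nominal 95% coverage for falls prevented is about 90-92% at a practice SD matching the protocol's ICC of 0.01 for any fall, and lower if the ICC is higher. If raw mean falls are used, falls prevented is 0.278 instead of 0.300 with equal 15% loss, and departs further in the cases of unequal loss shown.

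These sizes depend on assumed means, dispersion and mid-year loss; no ICC for costs is available. The effect at the planned ICC is modest, and restoring coverage depends on small-cluster scaling as well as on the resampling unit. The primary falls result is not affected. The change is worth making because it is cheap and the economic question is one of the listed effectiveness questions.

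**What to change.** State in the economic analysis that:
- the bootstrap resamples practices within arm (cluster or two-stage), with scaling for the small number of practices;
- each patient's costs and falls stay together in every replicate;
- falls prevented and costs are put on the same exposure-adjusted person-year basis as the primary falls analysis;
- the plane, the intervals and the acceptability curve are all drawn from these replicates.

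No new data are needed. The cost is a sentence or two of plan wording, a little more analysis work and somewhat wider intervals.

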### Multi-methodology implementation evaluation

While intervention researchers ask “does the proposed intervention” work, process evaluation is required to understand “how” it works [38]. This pragmatic approach using multi-methodology aims to understand fall prevention within the “real-world” setting [39], in this case, medical and allied health practice. The evaluation will also enable a deeper understanding of the coordinating role that the Primary Care Network can play in this area. In developing an intervention within an existing set of processes, referrals, and relationships (the GP and allied health settings), Normalization Process Theory (NPT) [31] can enable identification of facilitation factors. NPT focuses on the “work” of the intervention—and how changes in the work that is required to identify and refer people at risk of falls can become routinized into the everyday practice of the GP. NPT provides a framework for designing the inquiry and framing the interpretation of data.

#### In-depth interviews and surveys

The process of understanding implementation of the trial is iterative, seeking explanatory data at all layers, and over the entire time, of the intervention. Initial process evaluation will involve gathering data synchronistically with the intended intervention. Data will include surveys, in-depth interviews, observations and field notes, and documentation of meetings. Guided by NPT, we will examine the “coherence” of the proposed change for those in the work setting and how to facilitate the “collective action” needed to implement changes in practice, as follows:General practices. Data will comprise documentation of the academic detailing process and in-depth interviews with a sample of GPs and practice nurses participating in the intervention cluster. The aim is to elucidate how they perceive fall prevention as an issue for their patients; the barriers and facilitators to falls identification and to implementing fall management and referral practices; and how the iSOLVE resources are used (or not) and the perceived value of the education package and resources to changing practice.Allied Health Professionals (AHPs). AHPs are recruited to the workshops primarily thorough the SNHN website and newsletter. Other strategies have included professional association websites and interest groups, a Google™ search of service directories and service providers identified from GPs. AHPs are eligible if they are located in the geographical area of the SNHN, provide community services, provide or intend to provide fall prevention services to older people, and are able to receive GP referrals. A pre-, 3-, and 12-month post-workshop survey is administered following AHP education sessions and in-depth interviews conducted with a sample of AHPs participating in the workshops. The AHP implementation planning strategies compiled from data collected at the workshops will be used as an additional data source. The surveys include a combination of open-ended and Likert scale response questions; practice change, frequency of assessment and interventions related to fall prevention, referral patterns (to/from), type of services offered, and level of confidence in related skills. Demographic questions record profession, service sector, and nature of employment status. The interviews will ascertain the views of AHPs on any changes (or not) in the referral process; how effective the referral process is, and the factors affecting adoption and implementation of the intervention.

Interviews will also be conducted with key coordinating stakeholders, such as Primary Care Network staff. The views of these stakeholders will provide additional insights into the factors that may affect uptake of the intervention.

#### Survey across geographical area

A survey will be used to evaluate GP referral patterns and practices as markers of uptake and implementation across the intervention region, that is, the SHPHN. The survey comprises the same questions as in the trial survey for participating GPs Trends in program perceived efficacy, adoption, and implementation [40, 41] will be monitored over the 5 years of the program. The survey is being distributed annually to all GPs via the SNPHN mail lists in electronic format. As response rates are usually low for GPs [4], we are also randomly selecting 10% of all GPs in the region and mailing them a hard copy of the survey with pen. The random sample was selected using a computer-generated random permutation of integers.

#### Social network mapping

Relational data relating to the GPs professional network is being collected within the GP surveys as part of the cluster randomized trial. A question about who is influential is also included in the AHP survey and the area GP survey. Social network analysis is emerging as a potential tool to evaluate networks in healthcare settings [42, 43]. The network of roles from whom GPs develop their knowledge base in falls prevention will be visualized using an alluvial map generator. We will explore who in their social or professional networks have influenced their knowledge and learning of fall prevention and the depth of such influence, the people who they see as important in providing fall prevention services and if there are associations between these relationships and GP fall management and referral practices. An alluvial map can show how the impact of differing professional roles can change between, before, and after the academic detailing intervention [44].

The social network analysis of personal relationships with professionals who provide a clinical service to falls patients will first describe the structure of each network of referral relations. Second, it will explore the roles of other professionals relevant to their contribution to the GPs management of patients who had or are at risk of falls. In the second stage, we will quantify the contribution of relational processes that may have contributed to the structure of referral networks that we observed using exponential random graph models (ERGMs) and model the probability of a referral relationship formation. ERGMs provide statistical tests to assess if these effects are significantly different from zero [45]. Analogous to odds ratio in logistic regression models, model coefficients are interpreted as additive factors on the log odds of forming a relationship around referral. Significant and positive coefficients indicate higher log odds of forming a relation in accordance with the underlying process; negative coefficients make it less likely. The goodness of fit of each of these models will be assessed, following the procedures in Hunter et al. [46].

#### Implementation data analysis: surveys, observation data, and interviews

The information gathered will be used as indicative and descriptive information to inform further dissemination. Responses to survey data will be coded and compared within group and over time. Data will be explored using descriptive and graphical methods and, where possible, measure change in knowledge or practice using independent sample t tests and multinomial logistic regression. Documentation relating to the intervention (e.g., minutes of meetings, discussions with stakeholders) will be examined using content analysis. Analysis will focus on the “work of the intervention” [47]—how doing the work, concerns raised about the work, and how responsibility for falls prevention strategies is distributed across different groups. All interviews will be audio-recorded and transcribed verbatim. Thematic analysis (developing codes) will identify patterns within and across the study groups [48]. A combination of inductive and deductive coding will be used—coding will commence with examination of barriers and facilitators, but will be open to unexpected findings that may contribute to these. Data analysis will examine similarities and differences within and between stakeholder and participant groups and changes evident at different time points in the intervention [49].

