	What factors will influence sustainability of training and knowledge translation for GPs, AHPs and community pharmacist?	In-depth interviews of GPs and AHPs as above Pre- and post surveys of AHPs who participate in the workshops AHP planning strategies document from the workshops
	What is the GPs professional network in relation to fall prevention and who is influential within their network?	Relational network (who and influence) questions in survey for trial GPs. Network influence question in AHPs survey and in the ecological survey of GPs in geographical area of SNPHN
	How effective is iSOLVE dissemination across the SNPHN network?	Geographical survey of GPs in SNPHN

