#### Measures and data collection

Patient baseline data for control and intervention patients will include history of falls and fall injuries in the past 12 months, age, hospitalization in the past year, current medications, medication dosage and frequency, and comorbidities using the Functional Comorbidity Index [34]. Patients are asked to record falls using a prospective falls calendar to be completed on a daily basis and returned by mail monthly. Fall calendars also prompt patients to record the circumstances of a fall, whether any injuries occurred and whether any medical help was sought as a result of the fall. If a person does not return their fall calendar, they are telephoned to determine whether they have fallen. A 12-month follow-up survey ascertains patient engagement in fall prevention interventions or activities over the past year, interaction with GP about fall prevention, current medications including dosage and frequency. Medication survey questions will also generate data to determine prevalence and change over 12 months in medication exposures that have been associated with increased risk of falls with Drug Burden Index [35] as the major secondary measure. Other medication data will include polypharmacy, falls risk-increasing drugs [36, 37], and use of psychotropics (antipsychotics, antidepressants, and other mood stabilizers, benzodiazepines, and z-drugs) and other drug classes of interest.

The GPs complete a survey at baseline, 3 and 12 months, comprising a combination of open-ended and Likert scale response questions. The questions cover beliefs about fall prevention, knowledge of local fall prevention services, management of fall prevention and any changes in practice, and referral patterns.

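### The allied health professional survey re-surveys the same workshop attendees, but its change over time is to be tested with independent-sample t tests, which are conservative and lose power

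*Protocol article*

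**What the plan says.** Under the heading on implementation data analysis, the protocol article states the contrast: "Responses to survey data will be coded and compared within group and over time". It then says that, after descriptive and graphical exploration and where possible, the team will "measure change in knowledge or practice using independent sample t tests and multinomial logistic regression". The same paragraph opens by limiting the purpose: "The information gathered will be used as indicative and descriptive information to inform further dissemination".

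The AHP survey is described under In-depth interviews and surveys: "A pre-, 3-, and 12-month post-workshop survey is administered following AHP education sessions". Table 2 lists the same source as "Pre- and post surveys of AHPs who participate in the workshops", under the question on sustainability of training and knowledge translation. The article describes no group of AHPs who do not attend a workshop.

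Two other surveys matter for scope:
- **Trial GPs.** Under Measures and data collection, "The GPs complete a survey at baseline, 3 and 12 months". Their management score has its own analysis in the Data analysis plan: "The total score for each GP at 12 months will be compared between groups using regression analysis with baseline score as a covariate", with adjustment for clustering by practice.
- **GPs across the region.** Under Survey across geographical area, "The survey is being distributed annually to all GPs via the SNPHN mail lists in electronic format". A hard copy also goes to a random 10% of GPs. Whether a GP's answers can be linked from year to year is not stated.

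**The concern.** The independent-sample t test treats the two sets of answers as coming from unrelated people. In the AHP survey they come from the same attendees at different times, and the contrast of interest is each attendee's change. The test ignores the within-person correlation, so it uses the wrong standard error. This is not detail left to a fuller document, because the article names a specific test and that test does not match the design it describes.

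At stake is the reading of the AHP results. A test that is too conservative could report no change in knowledge or practice after the workshops when change had occurred. Treating waves as separate samples also means that the respondents remaining at 12 months are compared with everyone who answered at baseline, so dropout between waves can shift the comparison.

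**Working it through.** The article states no sample size, power or standard error for the implementation surveys, so there is no figure to reproduce.

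**Inputs from the article**
- AHP design: the same attendees before the workshop, at 3 months and at 12 months.
- Contrast: within group, over time.
- Named test: independent-sample t test.

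**Inputs assumed, because the article gives none**
- Equal SD at each wave, n complete pairs, two-sided 5% level.
- Within-person correlation rho of 0.3, 0.5 or 0.7.
- For power: a change of 0.3 SD with n = 50 or 100 (a second scenario, 0.4 SD with n = 50, is below).

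**Step 1: standard error**
- Independent-sample formula: SD × sqrt(2/n).
- Correct for paired data: SD × sqrt(2(1 − rho)/n).
- Ratio: 1/sqrt(1 − rho), whatever n is.

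**Step 2: true size of the nominal 5% test**

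Size = 2 × Phi(−1.96/sqrt(1 − rho)).

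| rho | SE ratio | True size |
|---|---|---|
| 0.3 | 1/sqrt(0.7) = 1.20 | about 1.9% |
| 0.5 | 1/sqrt(0.5) = 1.41 | about 0.6% |
| 0.7 | 1/sqrt(0.3) = 1.83 | about 0.03% |

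A simulation with 50 pairs and 20,000 replicates gave 2.0%, 0.6% and 0.04%; the paired test stayed close to 5%.

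**Step 3: power for a 0.3 SD change, rho 0.5**
- n = 50, independent test: the expected statistic is 0.3/sqrt(2/50) = 1.50, its true spread is sqrt(0.5) = 0.707, and the critical value is 1.984. Power is Phi((1.50 − 1.984)/0.707), about 25%.
- n = 50, paired test: noncentrality is 0.3/sqrt(2 × 0.5/50) = 2.12 on 49 degrees of freedom. Power is about 55%.
- n = 100, independent test: the expected statistic is 2.12 and the critical value 1.972. Power is Phi((2.12 − 1.972)/0.707), about 58%.
- n = 100, paired test: noncentrality is 3.00. Power is about 84%.

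At rho 0.3 the same steps give 28% against 42% (n = 50) and 57% against 71% (n = 100).

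**Step 4: a second scenario, by simulation** (0.4 SD, 50 pairs; independent against paired)
- rho 0: 51% against 50%, no material difference.
- rho 0.3: 51% against 65%.
- rho 0.5: 51% against 79%.
- rho 0.7: 52% against 95%.

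**Direction.** The error turns anti-conservative only if the correlation is negative. At rho −0.2 the SE ratio is 0.91 and the simulated size about 7.5%. Negative correlation is not what one expects when the same person answers the same items again.

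**The case against.** The strongest reply concerns weight. The article calls these data indicative and descriptive, puts graphical and descriptive methods first, and plans tests only where possible. No decision rule or sample size hangs on a survey p-value. Table 2 answers the primary implementation questions, on adoption and embedding, mainly from interviews, minutes, observations and planning documents; the AHP survey sits beside interviews under one further question. With positive correlation the error is conservative, so it would not manufacture a finding of practice change. All of this stands and lowers the priority. It does not make the named test fit: tests are still planned, and an indicative result also needs a correct standard error.

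It can also be said that an independent-sample test is valid for comparing change scores between separate groups. That is true, but the sentence just before the methods are named describes comparison within group and over time.

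Four stronger readings are tempting, and the article does not support them:
- **The multinomial model ignores the repeats and wastes ordinal information.** The article does not say that the model is fitted to pooled waves, nor that it is applied to Likert items. The surveys also hold coded open-ended answers, referral patterns and service types, which may be nominal.
- **The annual area GP survey has the same fault.** The mail lists are reused, so respondents may overlap, but recurrence is an inference. Low response is expected and linkage is not described. An independent-sample test may be the only practical option there.
- **Equal importance for implementation makes this a major flaw.** That statement covers the implementation evaluation as a whole, not this test.
- **The trial's outcomes are compromised.** The trial GP management score is adjusted for baseline, and falls and Drug Burden Index have separate analyses.

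**Conclusion.** The point holds for the AHP survey: the test named for change over time assumes independent samples, while the design re-surveys the same attendees. The direction, a standard error that is too large and a loss of power, holds for any positive within-person correlation. The size does not come from the article. Across assumed correlations of 0.3 to 0.7 the standard error is 1.20 to 1.83 times too large; in the assumed case of 50 attendees, 0.3 SD and rho 0.5, power falls from 55% to 25%. Those figures require linked, complete pairs with equal SDs. The consequence is modest and confined to an indicative analysis: it is worth correcting because correction is easy, not because it threatens the trial's conclusions.

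**What to change.** For AHP responses that can be linked across the three waves, replace the independent-sample t test with a paired test, or with a mixed model or GEE that has respondent as random effect or cluster and wave as fixed effect. For categorical items, state a method that also respects the repeats. Keep independent-sample tests only for waves that cannot be linked, which may include the annual area GP survey, and say so.

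The cost is a change of analysis wording, provided the AHP surveys carry an identifier. The article does not say whether they do, and the surveys appear to be under way. If early waves were anonymous, a linking code can serve only respondents not yet surveyed at baseline; the unlinked waves would keep the independent-sample test, with a note that it is probably conservative.
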